## Abstract

**Methods::**

children in pre-basic education in transition grades I and II (4 and 5 years old), and those in the first year of basic education (6 years old) will be invited to participate. The sample will be probabilistic. The measures of a randomized controlled trial (registered in ClinicalTrial.gov NCT04194580) will be used.

**Conclusion::**

the lack of reference values for physical condition and motor competence for children between 6 and 4 years of age in the Araucanía region highlights the need to establish values, which will contribute to improving the health of children of the age group to be worked on.

## 1. Introduction

Physical fitness is considered a measure that integrates most of the functions of the human organism that are involved in physical activity; its main components are cardiorespiratory endurance, muscular strength, speed-agility and flexibility.^[1]^ Scientific evidence indicates that presenting adequate physical fitness values are associated with health benefits such as having a healthier cardiovascular profile and lower risk of developing cardiovascular diseases throughout life^[2]^ improvements in mental health,^[3]^ decreased metabolic risk^[4]^ and total adiposity.^[5]^ Considering the aforementioned, it is convenient to include tests to assess the level of physical fitness of children in the school setting.^[6]^ Regarding Chile, there is a lack of indicators on physical fitness level in children aged 12 years or younger.^[7,8]^

Motor competence is defined as the degree of performance in a variety of motor tasks that are performed with good control and coordination of movements^[9]^ and is important due to its observed implications in the physical, mental and social development of children and adolescents.^[10,11]^ It is composed of fine and gross motor skills, the former being important in the academic and social fields^[10]^ and the latter as a basis for future motor competence.^[12]^ If children do not master these skills, they are likely to have limited opportunities to participate successfully in different physical activities throughout life.^[13]^ Delays or deficits in motor competence can affect fitness levels of children and adults.^[14]^

When considering early prevention of risk factors for noncommunicable diseases such as obesity, diabetes, cardiovascular diseases, among others, the assessment of physical fitness levels and motor competence is necessary for decision making aimed at promoting healthy behavior.

These assessments require the existence of updated reference values that allow the categorization of individuals and groups according to levels of physical fitness and motor competence, in addition to being established by sex since from early ages there are significant differences.^[15–18]^

Internationally, reference values have been established for children aged 4 to 6 years, both for physical fitness^[6,19,20]^ and motor competence.^[14,21]^ In Chile, the first reference values for physical fitness and motor competence in children aged 4 to 6 years were published in 2020^[22]^ which, being a contribution, has the limitation that the sample of 700 students was not representative of the region of La Araucanía, which does not allow inferences to be made to all students of similar age in the region.

Thus, this proposal arises from the need to improve the existing reference values, for which methodological strategies will be used to eliminate the limitations. The information provided by this study will serve as support for educational and health establishments, sports centers and parents, for the formulation of strategies that favor the adequate development of the variables studied in children from 4 to 6 years of age.

## 2. Objective

Effectiveness of a Physical Activity Intervention on the Overweight and Obesity of Chilean Schoolchildren, and in this way determine, through the calculation of a representative sample, reference values for physical fitness and motor competence in children aged 4 to 6 years in the region of La Araucanía, Chile.

## 3. Methods

### 3.1. Design

Non-experimental study, descriptive level and cross-sectional design, under a quantitative research approach, which will use the measurements of a randomized controlled trial registered in ClinicalTrial.gov (NCT04194580), whose objective is to evaluate the efficacy of an activity intervention physical therapy to prevent and treat obesity and excess weight in children aged 4 to 6 years.

### 3.2. Recruitment

For recruitment, an informative letter will be sent to educational establishments in the communes that make up the Araucanía region. The researchers will provide information about the objectives and methods of the study to the principal, school board and physical education teachers at the schools that agree to participate. The Scientific Ethical Committee of the Universidad Autónoma de Chile approved the study protocol (N°CEC 31-22).

### 3.3. Participants

In each establishment, children in pre-basic education in transition grades I and II (4 and 5 years old), and those in the first year of basic education (6 years old) will be invited to participate. Parents will be invited to an informative meeting where the researchers will provide the objectives and procedures of the study. The signing of an informed consent form by the parents will be mandatory for the children to participate. Information on each child’s parameters will be sent to the educational establishments as well as to the parents.

### 3.4. Inclusion and exclusion criteria

Once the sample calculation is estimated, which is detailed below, the following will be considered as inclusion criteria for schoolchildren: being enrolled in a school or college in the Araucanía region, belonging to the urban area, regardless of their administrative dependence; being in transition level I, II or first grade in 2022 and belonging to the age range of the study having authorization from the parents or legal guardians for the student’s participation in the research and that the children agree to participate in the study. The exclusion criteria for schoolchildren are suffering from pathologies that contraindicate the physical tests or that require special attention.

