## 4. Data analysis and management

### 4.1. Sample

Since the study will evaluate a representative sample of the Araucanía region, the sample size will be calculated according to the following criteria: total enrollment of students in transition I, II, and first grade in 2021; confidence level of 95%; margin of error of 5%; response rate of 80%. A sample 20% higher than the minimum will be established.

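### Eligibility is limited to urban pupils, but the objective, sample section and conclusion claim reference values for the whole region

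*Protocol article*

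**What the plan says.** The protocol article makes a regional claim in several places.

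- **Abstract, Methods:** "The sample will be probabilistic".
- **Section 1, Introduction:** of the reference tables published in 2020, it reports the following: "the sample of 700 students was not representative of the region of La Araucanía, which does not allow inferences to be made to all students". It adds that the new study will use methods meant to remove the limitations.
- **Section 2, Objective:** the study is to determine "reference values for physical fitness and motor competence in children aged 4 to 6 years in the region of La Araucanía, Chile".
- **Section 4.1, Sample:** "Since the study will evaluate a representative sample of the Araucanía region, the sample size will be calculated according to the following criteria". The first criterion is the whole 2021 enrolment in the three grades; no urban qualifier is attached.

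The eligibility rule is narrower. Section 3.4 requires "being enrolled in a school or college in the Araucanía region, belonging to the urban area, regardless of their administrative dependence".

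The Discussion (Section 5) says the earlier tables cannot be used for all children of similar age in the region, and its conclusion speaks of the region without qualification. The limitations it names are the cross-sectional design and the absence of other variables. The urban restriction is not among them.

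**The concern.** A reference table is only as general as the population it was drawn from. If part of the region's pupils cannot be selected, the table describes the rest, and calling it regional invites schools, health services and parents to apply it to children it does not cover. A rural child could then be classed as low or high in fitness or motor competence against urban percentiles, and nothing in the article would warn the user.

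The point is central because regional representativeness is the one advance over the 2020 tables that the article names. The eligibility rule removes the basis for that advance.

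**Working it through.** **Step 1. Set the statements side by side.**

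| Item | Section | Population |
|---|---|---|
| Target of the reference values | 2 | children aged 4 to 6 in the region |
| Claimed property of the sample | 4.1 | representative of the region |
| Enrolment used for the sample size | 4.1 | total, three grades, 2021 |
| Eligible pupils | 3.4 | urban area only |
| Stated limitations | 5 | urban restriction not mentioned |

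The wording of Section 3.4 leaves open whether the urban condition attaches to the school or to the child. Under either reading some of the region's pupils have selection probability zero. A sample cannot represent a population of which a part cannot enter, however the rest is drawn.

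**Step 2. Can the sample size repair this?** The article states no sample size, so there is no figure to reproduce. For context, take the usual precision formula with p = 0.5 (an assumption; the article gives no p), 95% confidence and a 5% margin:

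- n0 = 1.96² × 0.25 / 0.05² = 384.1, so 385 for a very large population.
- With a finite population N, n = n0 / (1 + (n0 − 1)/N). Enrolment is not stated; for assumed N of 5,000, 10,000 and 100,000 this gives 357, 370 and 383.
- From 385, dividing by the 80% response rate gives 482, and adding 20% to that gives 385 / 0.8 × 1.2 = 577.5, so 578.

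Two things follow. Changing the frame from total to urban enrolment hardly affects n: if urban enrolment were half of an assumed total of 10,000, n would fall from 370 to 357, a change of 13. And the selection probability of the excluded pupils stays at zero for every n, so a larger sample gives a more precise answer for urban pupils and none for rural ones.

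**Step 3. How large could the error be?** The documents give neither input, so this is only a range under assumptions: rural share r from 0.1 to 0.4, rural-urban difference d from 0.2 to 0.5 SD, normal distributions with equal SD.

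- Difference between the urban and the regional mean = r × d: from 0.1 × 0.2 = 0.02 SD to 0.4 × 0.5 = 0.20 SD.
- Share of the region's children below the urban 10th percentile, if rural children score lower = (1 − r) × 0.10 + r × Φ(−1.2816 + d). Lower end: 0.9 × 0.10 + 0.1 × 0.140 = 10.4%. Upper end: 0.6 × 0.10 + 0.4 × 0.217 = 14.7%. If they score higher, the shares are 9.7% to 7.5%.
- Among rural children alone, 14.0% to 21.7% would fall below the urban 10th percentile if they score lower, and 6.9% to 3.7% if they score higher.
- For comparison, the 95% half-width of a mean under simple random sampling is 1.96/√385 = 0.10 SD, or 1.96/√578 = 0.08 SD.

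At the lower end the error is negligible beside sampling error; at the upper end it is about twice as large.

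**The case against.** The strongest reply is that this is a condensed article, and that details of the sampling design may stand in a fuller protocol. That is a good answer to some stronger readings, but not to this point.

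- **That the sample is not a probability sample.** A reader might infer this because Section 3.2 describes letters to establishments and then refers to "physical education teachers at the schools that agree to participate". The text does not support it. Schools may have been drawn at random before the letters went out, and an article may leave that unsaid. Agreement is needed from randomly drawn schools too, and Section 4.1 allows for non-response with its 80% rate. Inviting whole grades within a drawn school is one-stage cluster sampling, a recognised probability design.
- **That the study repeats the 2020 limitation.** The Introduction says the earlier sample was not representative but not why. Only the consequence is the same, namely that the sample "which does not allow inferences to be made to all students of similar age in the region"; the cause may differ.
- **That the published percentiles will be materially biased.** Both inputs in the illustration above are assumed, and its lower end is trivial.
- **That the sample size is wrong because of the enrolment frame.** The frame does not match the eligible pupils, but the effect on n is small.

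These replies leave the urban restriction untouched. A random draw among urban schools would still give rural pupils no chance of selection, so no unseen detail of the draw reconciles Section 3.4 as printed with Sections 2, 4.1 and 5.

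**Conclusion.** The text is wrong as written on one point: Section 3.4 limits the study to urban pupils, while the objective, Section 4.1 and the conclusion claim the whole region and the limitations are silent. This conclusion rests on the printed statements alone and needs no numerical assumption beyond the region having some pupils outside the urban area, which the criterion itself implies.

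Its consequence is that the percentiles can support inference to urban pupils at most. The size of any resulting bias cannot be estimated from the document; the 0.02 to 0.20 SD shown above depends wholly on the assumed rural share and difference. Whether schools are drawn at random is a matter for clarification, not a demonstrated fault.

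**What to change.** 1. In the objective, Section 4.1 and the conclusion, state the target population as urban pupils of La Araucanía in the three grades, and say in Section 3.4 whether urban refers to the school or to the child.
2. In Section 4.1, use the matching urban enrolment as the frame.
3. In Section 5, list the exclusion of rural pupils as a limitation and say that the tables should not be taken to cover them.
4. Alternatively, keep the regional claim, but only if rural schools are admitted.
5. Confirm whether schools are drawn at random before the letters in Section 3.2 are sent. If they are not, remove the word probabilistic from the Abstract.

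Items 1 to 3 cost wording and an enrolment count restricted to urban pupils, with little effect on n. The price is a narrower claim than the one the article was written to make. Item 4 costs additional fieldwork. Section 3.5 places the measurements between September and December 2022, so if they have been completed without rural schools, narrowing the claim is the only option left.

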### 3.5. Outcome measures

The evaluations will be carried out between September and December 2022. They will be carried out by previously trained evaluators to ensure standardization.

Physical Condition: musculoskeletal capacity will be measured in the following criteria: upper body strength, through manual grip dynamometry; lower limb strength, through the standing long jump; speed-agility, through the 4 × 10 m test; cardiorespiratory capacity, will be measured through the Course-Navette test. These tests are part of the FITness in PREschoolers battery.^[23,24]^

Motor competence: will be measured through the Movement Assessment Battery for Children, in its second edition validated in Spanish,^[25]^ which has proven to be an instrument with adequate psychometric reliability properties (Cronbach’s α > 0.60; κ = 1; ICC = 0.85–0.99).^[26]^ This tool was developed for use in clinical and educational settings. The version with age range 4 to 6 years will be used, with the component’s manual dexterity, aiming and catching; balance (static and dynamic).

Anthropometric variables: weight will be obtained with a scale (Tanita MC-780U, Japan); height with a stadiometer (Seca 220, Germany); waist circumference, with a tape measure (Rosscraft, Canada); hip circumference, with a tape measure (Rosscraft, Canada). All variables will be measured twice, according to the protocol proposed by the International Society for Advances in Kineanthropometry.^[27]^ The average will be used for statistical analyses.

Body composition: Body mass index will be obtained through weight and height, as proposed by the World Health Organization.^[28]^ Waist-to-height and waist-to-hip ratios will be calculated to determine the level of central adiposity. Percentage body fat and fat-free mass will be measured using a bioimpedance analysis system (Tanita MC-780U, Japan).^[29]^

## 4. Data analysis and management

### 4.1. Sample

Since the study will evaluate a representative sample of the Araucanía region, the sample size will be calculated according to the following criteria: total enrollment of students in transition I, II, and first grade in 2021; confidence level of 95%; margin of error of 5%; response rate of 80%. A sample 20% higher than the minimum will be established.

### 4.2. Statistical analysis

The quantitative information collected will be tabulated in a database and analyzed using IBM SPSS Statistics 26. Descriptive values of frequencies, means and medians will be obtained according to the characteristics of the variables (continuous/discrete). The normality of the variables will be checked by means of graphs and the Kolmogorov-Smirnov test. Student *t* test or the Mann–Whitney *U* test (if the distribution is not normal) will be used to analyze differences between groups. In analyses involving more than 2 groups, analysis of variance or Kruskal-Wallis (if the data distribution is not normal) will be applied. Differences will be accepted considering a *P* value <.05. When statistically significant differences are found, the effect size will be calculated. Percentile values will be calculated using the least-mean-square algorithm method.^[30]^

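### The sample-size criteria and the named tests take no account of children being sampled through schools

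*Protocol article*

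**What the plan says.** **How children are reached.** Section 3.2 (Recruitment) sends a letter to educational establishments across the region and continues in those that consent. Section 3.3 (Participants) then works inside each school: "In each establishment, children in pre-basic education in transition grades I and II (4 and 5 years old" opens the sentence that invites these pupils together with the first year of basic education. The Abstract calls the sample probabilistic but gives no sampling stages, strata or number of schools.

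**How the sample is sized.** Section 4.1 takes as its population "total enrollment of students in transition I, II, and first grade in 2021" and adds "confidence level of 95%; margin of error of 5%; response rate of 80" per cent. It ends: "A sample 20% higher than the minimum will be established". No reason for the 20% is given, and it is not described as an allowance for clustering. No design effect, ICC, number of children per school or resulting sample size appears.

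**How groups are compared.** Section 4.2 uses the t test or Mann-Whitney for two groups. For more groups it says: "In analyses involving more than 2 groups, analysis of variance or Kruskal-Wallis (if the data distribution is not normal) will be applied". The threshold is P < .05. No school term, mixed model or complex-samples analysis is named, and the groups themselves are not listed. Percentiles come from a named algorithm with no stated measure of precision.

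**The concern.** Recruiting schools and then several children in each is cluster sampling. If children of one school are more alike than children of different schools, each further child from the same school adds less information than an independently drawn child would. The criteria in section 4.1 are those of a simple random sample of children, and all four tests in section 4.2 assume independent observations. Both therefore conflict with the recruitment described in sections 3.2 and 3.3.

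This matters because regional representativeness is the reason for the study. The Introduction faults the earlier 700-child reference values for not representing the region, and the 5% margin is the only precision that the article states for the new ones. With clustering, that margin is optimistic unless the within-school correlation is very small. A test on any factor that differs between schools would reject too often.

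**Working it through.** **No figure to reproduce.** The article gives criteria but no sample size, so the starting point is what its criteria imply.

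**Inputs from section 4.1:** 95% confidence (z = 1.96), 5% margin, 80% response, 20% surplus.

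**Assumptions, none in the document:** the margin applies to a proportion with p = 0.5; m children analysed per school; ICC from 0.02 to 0.10.

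**Step 1. Simple random sampling.** n = 1.96² × 0.25 / 0.05² = 384.2, so 385. The enrolment figure is not given. For an assumed 5,000 to 60,000 pupils, the finite-population correction lowers this to between 357 and 382, which changes little. Invited: 385 / 0.8 × 1.2 = 577.5, so 578. Analysed at 80% response: 385 × 1.2 = 462. This is the favourable reading, in which the surplus is fully realised.

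**Step 2. Margin with clustering.** Design effect = 1 + (m − 1) × ICC. Margin = 1.96 × 0.5 × √(design effect / n). At m = 20:

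| ICC | Design effect | Margin, n = 462 | Margin, n = 385 | Analysed n for a true 5% |
|---|---|---|---|---|
| 0.02 | 1.38 | 5.4% | 5.9% | 531 |
| 0.05 | 1.95 | 6.4% | 7.0% | 750 |
| 0.10 | 2.90 | 7.8% | 8.5% | 1,115 |

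For example, at ICC 0.05: 1.96 × 0.5 × √(1.95 / 462) = 0.064.

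**Step 3. What the surplus absorbs.** A 20% surplus offsets a design effect of 1.2, so (m − 1) × ICC = 0.2. This gives ICC = 0.2/9 = 0.022 at m = 10, 0.2/19 = 0.011 at m = 20 and 0.2/29 = 0.007 at m = 30.

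**Step 4. Type I error of a nominal 5% test, m = 20.** For a factor that varies only between schools: 2 × (1 − Φ(1.96 / √design effect)). For a factor balanced within schools: 2 × (1 − Φ(1.96 / √(1 − ICC))). The simulation used 24 schools of 20 children, t tests and 4,000 runs.

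| ICC | Between schools: formula (simulated) | Within schools: formula (simulated) |
|---|---|---|
| 0.02 | 0.095 (0.088) | 0.048 (0.049) |
| 0.05 | 0.160 (0.156) | 0.044 (0.046) |
| 0.10 | 0.250 (0.252) | 0.039 (0.042) |

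The error is inflated for between-school factors and slightly conservative for within-school ones.

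**The case against.** The strongest reply is that this is a condensed article: sampling stages, strata and the number of schools may stand in a fuller protocol. That excuses their absence here. It does not excuse the criteria and tests that the article does fix, because these do not fit the recruitment that it describes.

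Other replies limit the point, and they stand. A reader might infer more than the text supports in five ways:

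- *That confidence intervals or error bars are wrong.* The article plans none. It lists descriptive values, P values, effect sizes and percentiles.
- *That every comparison is invalid.* All four tests assume independence, but the harm depends on the contrast. Sex is the one grouping that the Introduction names for reference values. Boys and girls normally attend the same schools, so that comparison is nearly unaffected. No school-level comparison is named: administrative dependence appears only in the eligibility criteria, and communes only in recruitment. The inflated type I error applies only if such a comparison is made.
- *That the reference percentiles are biased.* Clustering alone does not bias the point estimates; it makes them less precise.
- *That all pupils of the three grades are taken.* Section 3.3 says children in those grades are invited, not that all are.
- *That the 5% margin is certainly missed.* ICC and school size are unknown. At a very low ICC, or with few children per school, the surplus keeps the margin at about 5%.

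**Conclusion.** The point holds in this limited form: the sample-size criteria and the named tests do not account for clustering by school. The direction is clear from the text; the size is conditional. With 20 children per school, p = 0.5 and 462 analysed, the real margin is about 5.4% to 7.8% over ICC 0.02 to 0.10, and the stated 5% survives only up to an ICC of about 0.011 (0.022 at 10 per school). A test on a between-school factor, if one is made, would have a type I error of about 9.5% to 25%; comparisons within schools are at or slightly below the nominal level. The percentiles, the main product, are less precise than the stated criteria imply. This should be fixed, but it does not invalidate the study.

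**What to change.** **Section 4.1.** State an assumed ICC and number of children per school, apply the design effect 1 + (m − 1) × ICC, and restate the margin of error actually delivered. Say whether the 20% surplus is meant to cover clustering.

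**Section 4.2.** Analyse with school as the cluster, through either a linear mixed model with a random intercept for school or a complex-samples analysis with school as the primary sampling unit. If confidence intervals are reported for the percentiles, obtain them by resampling whole schools.

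**Cost.** A little more analysis work and a less favourable stated margin. The analysis change can still be made after the September to December 2022 testing, provided each child's school is recorded. Restating the margin discloses the shortfall but does not remove it: holding a true 5% at 20 per school would take 531 to 1,115 analysed children over ICC 0.02 to 0.10, so no extra children are needed only if the wider margin is accepted.

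### Effect sizes are tied to P<.05, so those reported for group comparisons form a selected set, biased away from zero when the true differences are small

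*Protocol article*

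**What the plan says.** Section 4.2 (Statistical analysis) of the protocol article describes the group comparisons in sequence. A t test or Mann–Whitney test "will be used to analyze differences between groups". For several groups, "In analyses involving more than 2 groups, analysis of variance or Kruskal-Wallis (if the data distribution is not normal) will be applied". The threshold is then set: "Differences will be accepted considering a *P* value <.05". The next sentence is the rule at issue: "When statistically significant differences are found, the effect size will be calculated".

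Two other parts of the section limit the point. Summary statistics carry no significance condition: "Descriptive values of frequencies, means and medians will be obtained according to the characteristics of the variables (continuous/discrete". The percentile values are a separate calculation that uses neither P values nor effect sizes.

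Section 4.2 does not name the groups to be compared. Section 4.1 (Sample) gives criteria for calculating the sample size but no resulting number.

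**The concern.** An effect size that is calculated only after its own test has reached significance is a filtered estimate. Samples in which chance enlarged the difference pass the filter, and samples in which chance reduced it do not. If the true difference is small relative to its standard error, the effect sizes that reach the results table are on average too large. A comparison that misses .05 has no standardised measure to show whether the difference is negligible or merely imprecisely estimated.

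What is at stake is how the published group comparisons are read. Small differences will either look larger than they are or appear only as non-significant, which readers often take to mean absent. This is a rule that the article states, not a detail left to a fuller document.

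**Working it through.** The plan states no sample size, power or expected difference, so there is no figure of its own to reproduce. The question is how much the rule would distort effect sizes at plausible group sizes.

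**Inputs from the article.** Significance at .05 (Section 4.2; two-sided is my assumption). Sample criteria of 95% confidence, a 5% margin, 80% response and a 20% uplift (Section 4.1).

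**Assumed sample size.** For a large population and a proportion of 0.5 (assumed), the minimum is 1.96² × 0.25 / 0.05² = 384.1, so 385. With the 20% uplift it is 461. With division by 0.8 it is 481, and with both 577. A finite-population correction for an assumed enrolment of 5,000 to 50,000 lowers the minimum only to 357–382.

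**Assumed group sizes.** Two equal groups from 385, 461 or 577 children give about 192, 231 or 289 per group. Six equal cells (two sexes by three age years) give about 64, 77 or 96 per cell.

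**Formula.** Let d be the true standardised difference, n the number per group, SE = √(2/n) and m = d/SE. Treat the estimate as normal with mean d and standard deviation SE. It is significant when its absolute value exceeds 1.96 × SE. With U = Φ(m − 1.96) and L = Φ(−m − 1.96):

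- chance of significance = U + L
- mean absolute estimate, given significance = SE × [m(U − L) + φ(1.96 − m) + φ(1.96 + m)] / (U + L)
- inflation = that mean divided by d

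**Worked case.** For n = 192 and d = 0.2, SE = √(2/192) = 0.102 and m = 1.96. The chance of significance is 0.500. The mean significant estimate is 0.102 × (1.96 × 0.500 + 0.399) / 0.500 = 0.281. Inflation is 0.281 / 0.2 = 1.41.

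**Results.** Each cell gives the inflation factor, with the chance of significance in brackets.

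| n per group | smallest significant d | d = 0.1 | d = 0.2 | d = 0.3 | d = 0.5 |
|---|---|---|---|---|---|
| 64 | 0.35 | 4.25 (9%) | 2.23 (21%) | 1.57 (40%) | 1.12 (81%) |
| 77 | 0.32 | 3.89 (10%) | 2.05 (24%) | 1.46 (46%) | 1.08 (87%) |
| 96 | 0.28 | 3.51 (11%) | 1.86 (28%) | 1.35 (55%) | 1.04 (93%) |
| 192 | 0.20 | 2.54 (17%) | 1.41 (50%) | 1.10 (84%) | 1.00 (>99%) |
| 231 | 0.18 | 2.33 (19%) | 1.32 (58%) | 1.06 (90%) | 1.00 (>99%) |
| 289 | 0.16 | 2.11 (23%) | 1.22 (67%) | 1.03 (95%) | 1.00 (>99%) |

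The second column shows the gap in reporting: under the rule, no standardised difference below that value can appear. If every comparison is given an effect size, nothing is selected and the inflation factor is 1.0 throughout.

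The table covers two-group comparisons. The same selection acts on effect sizes that follow an analysis of variance or Kruskal-Wallis test, but I have not quantified it.

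**The case against.** The strongest reply is that the rule touches little of what the study is for. The product is a set of percentile values, and these are calculated without reference to any test. Means and medians are also obtained whatever the P value. It can be added that the sentence does not expressly forbid an effect size after a non-significant test, and that for moderate differences the inflation vanishes. Most of this stands, and it sets the limits of the point. It does not remove it: the natural reading of the sentence is that significance triggers the calculation, and small differences are where the distortion lies.

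A reader might infer more than the article supports, in four ways.

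- *That non-significant comparisons get no estimate at all.* The descriptive statistics are unconditional, although not stated to be by group. What the rule withholds is the effect size. Section 4.2 also describes no confidence interval, but that silence alone would not be a finding in a condensed article.
- *That all sex and age differences will be overstated.* The groups are not named in Section 4.2, so sex and age are inferences from elsewhere in the article. The inflation depends on power and is negligible for large differences.
- *That the rule decides whether separate tables are needed.* Nothing makes the tables depend on these tests. The Introduction already calls for reference values by sex: "in addition to being established by sex since from early ages there are significant differences".
- *That testing many outcomes without adjustment is part of the fault.* Section 3.5 lists 4 fitness, 3 motor, 4 anthropometric and 5 body-composition measures, 16 in all, and 1 − 0.95^16 = 0.56 would be the chance of at least one false positive if all nulls were true and independent. Independence fails here, because body mass index and the waist ratios are built from other listed measures. The lack of an adjustment rests only on the article's silence, and the number of tests does not cause the inflation.

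**Conclusion.** The point holds as one about reporting the group comparisons. The stated rule yields a selected set of effect sizes, biased away from zero when true differences are small, and leaves the other comparisons without one. At an assumed 190 to 290 per group, the bias is material at d of 0.1 to 0.2, slight at 0.3 (1.03 to 1.10 times) and absent at 0.5. In assumed subgroups of 64 to 96 it is still material at 0.3 (1.35 to 1.57 times) and small at 0.5.

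These figures rest on group sizes inferred from the sampling criteria, equal groups, a two-sided test and a normal approximation. The true differences are unknown. The direction of the bias depends on none of these choices; its size does. The percentile reference values are unaffected.

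**What to change.** Replace the conditional sentence in Section 4.2 with: *For every group comparison, the difference and effect size with 95% CI will be reported, regardless of the P value.* This removes the selection, and the interval shows whether a non-significant result excludes a difference worth knowing about. No further data or testing is needed. The cost is one sentence and additional table columns.
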